## Abstract

**Background:**

Hypoxia is one of the life-threatening complications of endotracheal intubation. Supplemental oxygen and ventilation play a vital role in preventing hypoxia. Bag-valve mask (BVM) ventilation is frequently used before intubation, and its ability to improve oxygenation was recently confirmed. It is still unclear if positive end-expiratory pressure (PEEP) added to BVM ventilation can further reduce hypoxia during intubation.

**Methods:**

This will be a prospective, randomized, double-blind trial to determine if PEEP combined with BVM ventilation can reduce the incidence of hypoxia during intubation compared with conventional BVM ventilation. The lowest oxygen saturation and incidence of complications will be compiled to verify the comparative effectiveness and safety of the two groups.

**Discussion:**

BMV ventilation with PEEP is hoped to further reduce the incidence of hypoxia during intubation.

**Trial registration:**

Chinese Clinical Trial Registry ChiCTR2000035156. Registered on August 2, 2020. It had begun enrollment after passing ethical review but before registration.

Role of sponsor {5c}	The study sponsor and funders helped with the design of the study and collection, analysis, and interpretation of data and in writing the manuscript. They will have ultimate authority over any of these activities.

### Composition of the coordinating center and trial steering committee {5d}

The endpoint adjudication committee is composed of the heads of each hospital and will take counsel together to decide whether to terminate the study early.

## Introduction

### Background and rationale {6a}

Endotracheal intubation is a critical emergency medical procedure for patients who are unable to maintain adequate oxygen saturation or a patent airway. However, serious adverse events such as hypoxia, hypotension, aspiration, or cardiac arrest can occur during intubation. Among them, hypoxia is one of the most common complications in the emergency department (ED) [1–3]. This proportion is much higher than that seen in the operating room [4] because ED patients are most likely suffering from pathophysiological lung disease without the luxury of fasting or extensive pre-operative screening tests. Furthermore, hypoxia may reduce the first pass success of intubation [5] and associate with cardiac arrest [6]. It is therefore vital that we find better tools to reduce hypoxia during intubation in the ED.

A bag-valve mask (BVM) is a frequently used, portable, and economical ventilation device for improving patients’ oxygen saturation before intubation in the ED. The advantage of using BVM ventilation in different scenarios has been shown in multiple studies [7–9]. Additionally, a new randomized, controlled study of BVM ventilation demonstrated a decreased incidence of desaturation during intubation using BVM while not increasing the risk of aspiration or hypotension compared with no BVM ventilation [10, 11]. It remains unclear whether the effectiveness of BVM ventilation can be further improved, however. As a result, this trial will focus on the amelioration of BVM ventilation.

Applying a positive end-expiratory pressure (PEEP) valve to the BVM device allows for PEEP to be applied during BVM ventilations, potentially increasing the efficacy of BVM ventilation [12]. Before intubation, pre-oxygenation is routinely performed to improve a patient’s oxygen reserve and postpone the onset of hypoxia [13, 14]. Unfortunately, a high concentration of inhaled oxygen may also cause absorption atelectasis. The use of PEEP is one of the more effective ways to cope with atelectasis by preventing the collapse of the lung’s alveoli [15].

As we have already known, hypoxia commonly occurs and has a negative impact. BVM ventilation is widely used and shows few side effects. Although the utility of prophylactic BVM ventilation for patients with acute respiratory failure in the ICU has been demonstrated, few trials have assessed different BVM ventilation methods. This study will concentrate on the improvement of BVM ventilation to reduce hypoxia. It will verify whether adding PEEP to prophylactic BVM ventilation for ED patients during the intubation is superior to BVM alone in reducing hypoxia. This trial will be a randomized, double-blind, controlled trial to compare the effectiveness of BVM ventilation with or without PEEP. We hypothesize that BVM ventilation with PEEP may increase patients’ oxygen saturation and lower the risk of hypoxia.

### Explanation for the choice of comparators {6b}

Patients allocated to the control group will be ventilated using conventional BVM ventilation. All other patient characteristics and interventions will be the same as the intervention group.

## Objectives {7}

### Primary objective

To determine whether additional PEEP with BVM ventilation could improve the ventilation efficiency and lower the hypoxia compared with merely BVM ventilation in ED patients undergoing intubation. Hypoxia is defined as an oxygen saturation lower than 90%.

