### Outcomes {12}

#### Primary outcome measure

The primary outcome measure is the lowest oxygen saturation recorded via pulse oxygen saturation monitoring during the intubation procedure. The intubation procedure starts when the laryngoscope blade is inserted and ends once the endotracheal tube position is confirmed. Since there may be further delays of the pulse oxygen saturation, data will continue to be recorded until 2 min after intubation ends.

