#### Secondary outcome measures

The secondary outcomes deal with respiratory and circulatory complications. We will focus on two of these (severe hypoxia and aspiration) in terms of respiration. The number of patients whose pulse oxygen saturation is lower than 80% during the intubation procedure and the incidence of aspiration will be recorded. Aspiration is defined as the observation of stomach contents at the aditus glottidis by a laryngoscope during the intubation. As for circulation, we will pay close attention to the lowest systolic blood pressure reading, the number of patients with systolic arterial blood pressure lower than 90 mmHg, and any cases of cardiac arrest.

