#### Analysis of secondary outcomes

The frequency and incidence rate of relevant complications, including SpO_2_ less than 80%, aspiration, systolic arterial blood pressure less than 90 mmHg, cardiac arrest, will be calculated in both groups. Then, based on the number of complications, select the chi-square test or Fisher’s exact probability test for comparison.

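### The trial asks whether PEEP reduces hypoxia, defined as saturation below 90%, but no outcome or analysis counts patients below 90%

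*Protocol article*

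**What the plan says.** **The question.** The abstract (Methods) says the trial is meant "to determine if PEEP combined with BVM ventilation can reduce the incidence of hypoxia during intubation compared with conventional BVM ventilation". The primary objective in Objectives {7} asks whether adding PEEP "could improve the ventilation efficiency and lower the hypoxia compared with merely BVM ventilation", and then sets the threshold: "Hypoxia is defined as an oxygen saturation lower than 90" per cent. The hypothesis that closes the background section is that PEEP "may increase patients’ oxygen saturation and lower the risk of hypoxia". Trial design {8} also describes the aim as preventing hypoxia.

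**The outcomes.** Under Outcomes {12}, "The primary outcome measure is the lowest oxygen saturation recorded via pulse oxygen saturation monitoring during the intubation procedure". Among the secondary outcomes, respiration is limited to two items, severe hypoxia and aspiration: "The number of patients whose pulse oxygen saturation is lower than 80% during the intubation procedure and the incidence of aspiration will be recorded".

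**The analyses.** Lowest SpO2 is compared by independent-sample t-test or rank-sum test, depending on distributional checks. Under Analysis of secondary outcomes, the complications to be tabulated and tested are introduced by "The frequency and incidence rate of relevant complications, including", and the list that follows is SpO2 below 80%, aspiration, systolic pressure below 90 mmHg and cardiac arrest. The 90 in that list is a blood pressure, not a saturation.

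**The concern.** The objective defines an event by a threshold, and the abstract and hypothesis speak of its incidence or risk. An incidence is a proportion of patients. None of the planned analyses estimates the proportion below 90%, so the definition in the primary objective is never used.

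Lowest SpO2 and the proportion below 90% are related but not interchangeable:

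- If patients who would have reached a low of 92% reach 97% instead, a t-test or rank-sum test can be significant while the number below 90% stays the same.
- A few very low values in one arm can move a mean without changing how many patients cross 90%.
- Patients can cross 90% in fair numbers without a significant shift in the whole distribution.

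At stake is the headline claim. If the trial succeeds on lowest SpO2 and the report says that hypoxia was reduced, no prespecified analysis at the protocol's own threshold supports that sentence. If the 90% count is added once results are known, it is a post hoc cut-point beside a prespecified one at 80%.

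**Working it through.** **Step 1: question against analysis**

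| Element | Section | Quantity |
|---|---|---|
| Aim | Abstract, Methods | Incidence of hypoxia |
| Hypothesis | Background and rationale {6a} | Saturation, and risk of hypoxia |
| Primary objective | Objectives {7} | Ventilation efficiency, and hypoxia at <90% |
| Primary outcome | Outcomes {12} | Lowest SpO2, continuous |
| Secondary saturation outcome | Outcomes {12} | SpO2 <80% |
| Primary test | Statistical methods {20a} | t-test or rank-sum on lowest SpO2 |
| Secondary saturation test | Statistical methods {20a} | Chi-square or Fisher on SpO2 <80% |

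No row from the outcomes downward uses 90% saturation. The finding rests on this table alone; what follows only indicates scale.

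**Step 2: the plan's own figure**

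Inputs from Sample size {14}: control mean 88, increase 5, SD 12, two-tailed α 0.05, β 0.20, 72 per arm.

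n per arm = 2 (z_α + z_β)² σ² / δ², with σ²/δ² = 144/25 = 5.76.

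- Two-sided: 2 × (1.960 + 0.842)² × 5.76 ≈ 90.4, so 91 per arm (92 with the noncentral t).
- One-sided: 2 × (1.645 + 0.842)² × 5.76 ≈ 71.2, so 72 per arm.

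The stated 72 does not reproduce as two-tailed; it matches a one-sided 0.05 test. At 72 per arm, two-sided power for the mean difference is about 70%. That is a separate matter, but 70% is the benchmark for the power figures below.

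**Step 3: what the planning figures imply for <90%**

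Assumption: lowest SpO2 is normal with means 88 and 93 and SD 12.

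- Control: Φ((90 − 88)/12) = Φ(0.167) = 0.566
- PEEP: Φ((90 − 93)/12) = Φ(−0.25) = 0.401
- Difference: 0.165
- 95% CI half-width at 72 per arm: 1.96 × √[(0.566 × 0.434 + 0.401 × 0.599)/72] = 1.96 × 0.082 ≈ 0.161
- Power, pooled variance under the null: Φ((0.1649 × √72 − 1.960 × √(2 × 0.4837 × 0.5163)) / √(0.4859)) = Φ((1.399 − 1.385)/0.697) = Φ(0.02) ≈ 0.51
- Size for 80% power: 144 per arm

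For <80% under the same model: Φ(−8/12) = 0.252 and Φ(−13/12) = 0.139, with power about 0.40 at 72 per arm.

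**Step 4: sensitivity to the SD, <90%**

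| SD | Control | PEEP | Power at 72 per arm | n per arm for 80% |
|---|---|---|---|---|
| 8 | 59.9% | 35.4% | 84% | 65 |
| 10 | 57.9% | 38.2% | 66% | 100 |
| 12 | 56.6% | 40.1% | 51% | 144 |
| 15 | 55.3% | 42.1% | 35% | 223 |

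**The case against.** The strongest reply is that the protocol is consistent where it counts. Primary outcome, sample size and primary test all use lowest SpO2. The hypothesis names higher saturation before it names risk of hypoxia, the objective also names ventilation efficiency, and the abstract says that lowest saturation will be used to judge effectiveness. Only the abstract uses the word incidence for hypoxia. A continuous primary outcome is legitimate and more efficient: about 70% power against about 51% at 72 per arm under the same model. One hypoxia incidence, at 80%, is prespecified, and the 90% count can be derived at any time from recorded values. The planned means straddle 90, so the planned effect would itself reduce the proportion below 90%.

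Much of this is right. Lowest SpO2 should remain primary, and nothing in data collection is at fault. It would also be too strong to say that the trial could never report the 90% incidence; it simply has no prespecified analysis of it. But speaking of lowering hypoxia, or its risk, next to a threshold definition is still a statement about how many patients cross the threshold. The open wording of the complication list does not bring in <90%, because its items are those of the secondary outcomes section, which confines respiration to severe hypoxia and aspiration.

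The objection to the normal model also stands in part. It puts about 16% of control and 28% of PEEP patients above 100% saturation, which is impossible, and SpO2 is usually left-skewed. The percentages are illustrative only.

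**Conclusion.** The concern holds. The protocol defines hypoxia as saturation below 90% in its primary objective and then analyses only continuous lowest SpO2 and SpO2 below 80%. This is a contradiction between stated parts of the document, not detail left to an analysis plan.

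It is a point that should be corrected, not one that invalidates the primary analysis. On the planning figures and a normal model, the undefined comparison would be roughly 57% against 40%, with an interval half-width about as large as the difference. Success on lowest SpO2 therefore cannot be assumed to carry over to a clear result on hypoxia incidence. These sizes depend on the assumed SD and on treating the quoted mean saturation as the mean of the lowest SpO2; the mismatch does not.

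**What to change.** Before unblinding:

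1. List the proportion of patients with lowest SpO2 below 90% as the first secondary outcome, in both Secondary outcome measures and Analysis of secondary outcomes, reported as a risk difference with 95% confidence interval.
2. Keep lowest SpO2 as the primary outcome and word the primary conclusion in those terms.
3. State that any claim of reduced hypoxia incidence rests on the new outcome, and acknowledge that its interval is likely to be wide at 72 per arm.

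Rewording the abstract and objective to ask only about lowest saturation would also remove the contradiction, but it would leave the question that the protocol sets out unanswered. Making <90% the primary outcome is not proposed; it would need a new sample size.

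The cost is one further analysis and some wording. The lowest SpO2 is already recorded for every patient under the data collection plan {18a}, so no new data are needed.

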### Secondary objectives

The incidence of complications associated with BVM with or without PEEP, such as aspiration, hypotension, or cardiac arrest during intubation. Aspiration is defined as the presence of vomit seen in the glottic region during intubation. Hypotension is defined as a mean blood pressure lower than 65 mmHg.

### Trial design {8}

This will be a prospective, randomized, parallel group, controlled, double-blind, superiority trial to compare the effectiveness of BVM ventilation with or without PEEP to prevent hypoxia during intubation.

## Methods: participants, interventions, and outcomes

### Study setting {9}

This study will be led by the Emergency Department of Peking Union Medical College Hospital in Beijing, China. Three other hospitals will also enroll patients, including the First Affiliated Hospital of Xinjiang Medical University in the Xinjiang Uygur Autonomous Region, the Second People’s Hospital of Huai’an, and the Suqian People’s Hospital in Jiangsu province in China. These are all grade III A hospitals with adequate medical consultants, qualified doctors, and monitoring equipment to fulfill this study.

### Eligibility criteria {10}

#### Inclusion criteria

Patients requiring endotracheal intubation in the ED for acute respiratory failure will be recruited. Acute respiratory failure is defined as a respiratory rate higher than 30 breaths per minute, dyspnea at rest, a partial arterial oxygen pressure (PaO_2_) less than 60 mmHg on room air, or a PaO_2_ divided by the fraction of inspired oxygen (FiO_2_) less than 300 regardless of supplemental oxygen provided.

#### Exclusion criteria

Patients who are pregnant, less than 18 years old, or unwilling to participate in the study will be excluded. Patients with acute circulatory failure, cardiac arrest before intubation, anticipated difficult airway, chronic hypoxemia, or difficult BVM ventilation will be excluded as well.

Acute circulatory failure is defined as hypotension requiring vasopressor therapy to maintain a mean blood pressure more than 65 mmHg [16]. A difficult airway will be evaluated using the MACOCHA score, described in detail as Mallampati score III or IV, apnea syndrome (obstructive), cervical spine limitation, opening mouth less than 3 cm, coma, hypoxia, and anesthesiologist nontrained. A score less than 3 could almost exclude the difficult airway [17]. Difficult BVM ventilation means that it is not possible to provide adequate ventilation due to one or more of the following problems: inadequate seal, excessive gas leak, or excessive resistance to ingress or egress of gas [18].

#### Dropout criteria

Patients enrolled in this study quit for whatever reason before the ending or their data miss too much to analyze. Either situation could drop out the subjects.

Before the study, investigators will be trained to gather information timely and thoroughly explain the research process and related details to lower the possible dropouts.

## Interventions

### Intervention description {11a}

The settings for both groups are the same except for the extra PEEP. Oxygen flow rates will both be set at 15 l/min. The two-person, two-handed method will be used by two experienced ED providers in order to achieve an adequate seal [19, 20]. Ventilation will proceed at 12–20 breaths per minute until intubation. During this process, vital signs and other information will be recorded by staff trained in the research protocol.

### Criteria for discontinuing or modifying allocated interventions {11b}

Patients could opt out of the study at any time. If hypotension, reflux aspiration, or other possible adverse reactions occur during BVM ventilation, we will stop and take corresponding measures to treat any adverse reactions.

### Strategies to improve adherence to interventions {11c}

We hope to reduce any episodes of hypotension due to excessive lung expansion by controlling ventilation through appropriate monitoring. Gastric intubation and suction will be performed to reduce the incidence of aspiration, depending on fasting time.

### Relevant concomitant care permitted or prohibited during the trial {11d}

Non-invasive ventilation will not be used during the trial. Other airway interventions are permitted and will be noted on the study data form.

### Outcomes {12}

#### Primary outcome measure

The primary outcome measure is the lowest oxygen saturation recorded via pulse oxygen saturation monitoring during the intubation procedure. The intubation procedure starts when the laryngoscope blade is inserted and ends once the endotracheal tube position is confirmed. Since there may be further delays of the pulse oxygen saturation, data will continue to be recorded until 2 min after intubation ends.

#### Secondary outcome measures

The secondary outcomes deal with respiratory and circulatory complications. We will focus on two of these (severe hypoxia and aspiration) in terms of respiration. The number of patients whose pulse oxygen saturation is lower than 80% during the intubation procedure and the incidence of aspiration will be recorded. Aspiration is defined as the observation of stomach contents at the aditus glottidis by a laryngoscope during the intubation. As for circulation, we will pay close attention to the lowest systolic blood pressure reading, the number of patients with systolic arterial blood pressure lower than 90 mmHg, and any cases of cardiac arrest.

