## Data collection and management

### Plans for assessment and collection of outcomes {18a}

Before randomization, some basic information will be recorded: patient identification number, age, sex, height, weight, body mass index, primary diagnosis, reason for intubation, systolic blood pressure, vasopressor use before intubation including the type and dosage, and any oxygen therapies used, including FiO_2_ and duration of use, pulse oximetry (SpO_2_) before intubation, and recent blood gas analysis (pH, PaO_2_, arterial carbon dioxide partial pressure (PaCO_2_)); any history of a difficult airway, airway evaluation using the MACOCHA score, and the time since the patient’s last meal will be recorded.

According to this basic information, patients who meet eligibility criteria will be randomized. A member of the research staff will select the corresponding BVM device for use prior to intubation. During the procedure, another member of the research staff will record key data. For example, the induction medicine (including drug name and dosage), the duration of BVM ventilation, the SpO_2_ before inserting the laryngoscope, the duration between inserting the laryngoscope and 2 min after intubation, the number of intubation attempts, the lowest SpO_2_ during the procedure, the lowest systolic blood pressure, any vasopressor use, and any incidence of aspiration or cardiac arrest.

During prophylactic BVM ventilation, some additional parameters will be monitored. Data such as exhaled tidal volume, respiratory rate, exhaled oxygen concentration, and partial pressure of end-tidal carbon dioxide will be collected to guarantee consistent manipulation and avoid bias caused by improper operation.

Intubation will be performed by physicians with at least 3 years of previous intubation experience to ensure patient safety. All data will be recorded in the Case Record Form and managed by the ResMan clinical trial public management platform. After collection, data will be analyzed by the statistician in our research group.

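### Vasopressor use during the procedure is recorded but enters no circulatory safety outcome, so patients kept at or above 90 mmHg by treatment are not counted

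*Protocol article*

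**What the plan says.** Under Secondary outcome measures, the protocol article lists three circulatory outcomes: the lowest systolic pressure, "the number of patients with systolic arterial blood pressure lower than 90 mmHg, and any cases of cardiac arrest". Under Analysis of secondary outcomes, the complications compared by chi-square or Fisher's exact test are severe desaturation and "aspiration, systolic arterial blood pressure less than 90 mmHg, cardiac arrest, will be calculated in both groups". That section names no test for the lowest systolic pressure, and neither section mentions vasopressors.

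The data collection section (item 18a) does. Before randomisation it records "vasopressor use before intubation including the type and dosage". During the procedure it records "the lowest systolic blood pressure, any vasopressor use, and any incidence of aspiration or cardiac arrest". Of the four items in that last list, vasopressor use is the only one that is not an outcome.

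Three other places bear on the point:
- Exclusion criteria: "Acute circulatory failure is defined as hypotension requiring vasopressor therapy to maintain a mean blood pressure more than 65 mmHg". Such patients are not enrolled.
- Item 11b: if hypotension or another adverse reaction occurs during BVM ventilation, "we will stop and take corresponding measures to treat any adverse reactions".
- Items 21b and 22: the study stops early for clear harm in the intervention group, with a significantly higher complication rate as the example. The check is at 6 months.

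**The concern.** Hypotension is a harm that the protocol foresees. Item 11c mentions it as a consequence of over-expanding the lungs, and PEEP could plausibly add to that. An outcome that looks only at the pressure reached is altered by whatever is done to support the pressure. Two patients with the same circulatory response can be scored differently: one untreated who reaches 86 mmHg is counted, and one given a vasopressor who bottoms out at 92 mmHg is not.

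The entry criteria handle this differently. There, a pressure that needs a vasopressor is itself circulatory failure. After randomisation, need for the same support counts for nothing.

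At stake are the safety comparison and the 6-month check. If complications are tallied there from the analysis list, that check has the same blind spot.

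**Working it through.** **1. The outcome definition.** Set the three lists side by side.

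| Item | Recorded (18a) | Outcome | Test named |
|---|---|---|---|
| Lowest systolic pressure | yes | yes | no |
| Systolic <90 mmHg | derived from the lowest reading | yes | yes |
| Cardiac arrest | yes | yes | yes |
| Vasopressor use during the procedure | yes | no | no |

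The patients affected are those who receive a vasopressor and whose lowest reading stays at or above 90 mmHg. The continuous outcome does not close the gap, because treatment raises it as well. The mean-pressure definition under Secondary objectives, "Hypotension is defined as a mean blood pressure lower than 65 mmHg", has no vasopressor term either. Its mismatch with the systolic cut-off is a separate matter.

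**2. Size.** The protocol gives no expected rate of hypotension or vasopressor use, so there is no figure of its own to reproduce for this outcome. The inputs taken from it are 72 per arm (Sample size, calculated for the primary outcome) and two-sided 0.05. The event rates and masked shares below are assumptions.

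Let p be the true rate of circulatory compromise in an arm and m the share kept at or above 90 mmHg by treatment. The observed rate is p(1 − m).

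*Scenario A: 30% with PEEP, 15% without, m = 0.20 in both arms.*
- Observed: 0.30 × 0.80 = 24% and 0.15 × 0.80 = 12%.
- The difference falls from 15 to 12 points. The ratio stays at 2.0.
- Patients not counted: 72 × 0.06 = 4.3 with PEEP and 72 × 0.03 = 2.2 without.
- Power = Φ[(d − 1.96·SE0)/SE1], where SE0 uses the pooled rate and SE1 the separate rates.
- All counted: SE0 = √(2 × 0.225 × 0.775/72) = 0.0696; SE1 = √((0.30 × 0.70 + 0.15 × 0.85)/72) = 0.0685; (0.15 − 0.1364)/0.0685 = 0.20; power 58%.
- Masked: SE0 = 0.0640; SE1 = 0.0632; (0.12 − 0.1255)/0.0632 = −0.09; power 47%.

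*Scenario B: 25% with PEEP, 10% without, m = 0.50 in both arms.*
- Observed: 12.5% and 5%.
- The difference falls from 15 to 7.5 points. The ratio stays at 2.5.
- Patients not counted: 72 × 0.125 = 9 with PEEP and 72 × 0.05 = 3.6 without.
- Power = Φ(d/SE − 1.96), with separate rates throughout.
- All counted: SE = √((0.25 × 0.75 + 0.10 × 0.90)/72) = 0.0621; 0.15/0.0621 = 2.42; power 68%.
- Masked: SE = √((0.125 × 0.875 + 0.05 × 0.95)/72) = 0.0467; 0.075/0.0467 = 1.61; power 36%.

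Exchanging the two power formulas changes little: A becomes 59% and 47.5%, B becomes 66% and 36%.

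Equal masked shares leave the risk ratio alone. They still remove more patients from the arm with more events, so the absolute difference and the power fall.

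**The case against.** The case on the other side has several parts, and much of it stands.

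- A reader might infer that every patient supported by a vasopressor scores as free of complication. That is not so. The outcome uses the lowest reading, so anyone who falls below 90 mmHg before treatment is counted. Item 11b describes action after hypotension has occurred and does not name vasopressors. Only early treatment escapes the count. Recording vasopressor use during the procedure shows that it is foreseen, but not how often it would come early.
- A reader might infer that masking is relatively heavier under PEEP. With 20% masked in control and 50% under PEEP, scenario A would show 12% vs 15%, with power of about 8%. The documents give no basis for unequal shares. Item 17a blinds those ventilating and intubating, with devices of identical appearance, so there is no stated reason for treatment thresholds to differ by arm.
- The lowest systolic pressure is an outcome, so a fall to 92 mmHg is not lost, and systolic pressure before randomisation is also recorded. This is a partial safeguard, but treatment blunts the reading and no test is named for it.
- The stopping wording is open: a higher complication rate is only an example. A reader might infer that the 6-month check is bound to the listed counts. Nothing says so, and nothing bars the committee from looking at vasopressor data. Equally, nothing puts those data in front of it.
- The protocol mentions hypotension alongside aspiration and does not rank it as the chief expected harm.
- An unseen analysis plan could tabulate vasopressor use. The article nevertheless states its circulatory outcomes and its complication list, and vasopressor use is in neither.

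**Conclusion.** The point holds in a limited form. A circulatory response that is treated before systolic pressure reaches 90 mmHg is not counted, and the recorded item that would reveal it is used nowhere. If PEEP lowers pressure, the effect is a smaller absolute difference and a lower chance of seeing harm.

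How much smaller cannot be derived from the documents. The illustrations run from a loss of 11 percentage points of power (58% to 47%) to 32 (68% to 36%), and both rest on assumed rates and masked shares. They do not support a claim that harm would be hidden almost entirely or that the relative risk would be distorted. The primary outcome is unaffected. This is a cheap improvement to a secondary safety comparison and to the information available at the harm check.

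**What to change.** Keep the existing circulatory outcomes. In Secondary outcome measures and Analysis of secondary outcomes, add a comparison between arms of new vasopressor use from the start of BVM ventilation to 2 minutes after intubation. Report it on its own and within a composite of systolic pressure below 90 mmHg, new vasopressor use, or cardiac arrest, with every component shown separately. Include the same counts in the material reviewed at 6 months (items 21b and 22).

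On the existing form item, note the start time and the reason, so that prophylactic use can be told from treatment of a fall. The vasopressor record taken before randomisation already allows new use to be identified.

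The cost is wording and two small additions to one form item. The downside is that vasopressor use is partly at the clinician's discretion and some starts will be prophylactic, which would dilute the composite. Showing the components deals with the dilution, and staff blinding limits bias from discretion. No treatment or clinical rule changes.
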